**Figure 1 F1:**
[figure not shown]
Lyprinol protocol flow diagram.

#### Randomization and safety

Randomization of participants to treatment groups will be determined by random allocation. All 150 participants will be assigned to treatment group A or B using a computer generated random number generator by a neutral third party. Eligible, recruited participants will be assigned a participant number. The treatment number that has been placed next to the participant’s number will be the allocated treatment for that individual. Blinding will be achieved by enlisting a person outside of the project to code the treatments, and maintain the key to this code until data collection is completed. An emergency code break envelope will be provided to the principle investigator which will only be opened in case of emergency. Participants’ parents will also be given a weekly symptom checklist to complete to monitor for any adverse events. Researchers will be blinded to the treatment conditions.

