### Design

The study is a randomized, double-blind, placebo-controlled, 2-armed, parallel groups clinical trial with children and adolescents randomized to receive either 3 capsules (if less than or equal to 45 kg) or 4 capsules (if greater than 45 kg) of PCSO-524® or placebo.

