#### Power and statistical analysis

The sample size for this study is 150 participants with 75 participants in each arm (Lyprinol vs Placebo). A power calculation to determine the sample size was performed using Gpower 3.12. Based on previous studies looking at omega-3 supplementation in children with ADHD such as Sinn & Bryan (2007) who had an *n* of 132 and were able to find statistical significance in terms of the CPRS [15], a small to medium effect size (F = .20) on the Conners’ was postulated for Lyprinol over placebo from baseline to week 18 over six time points (critical F = 3.92, with an alpha probability of 0.05 and beta power of 0.80). This provided a sample size of 118; with drop-outs being projects at approximately 20%, a sample of 150 participants was estimated. Repeated Measures ANOVAs with an *n* of 150 (75 per group) will allow the researchers to account for any confounding variables in the trial including within-group and between-group variability. Any heterogeneous variables showing statistically significant differences at baseline will be co-varied in order to negate their influence on the power of the study.

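### Neither the stated allocation nor the stated analysis uses the 45 kg weight split, and the baseline-significance rule for covariates would let moderate chance imbalances in it go unadjusted (minor)

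*Protocol article*

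**What the plan says.** Under *Randomization and safety* the article gives the whole allocation method: "All 150 participants will be assigned to treatment group A or B using a computer generated random number generator by a neutral third party". It adds that "The treatment number that has been placed next to the participant’s number will be the allocated treatment for that individual". It does not say whether the list is simple, blocked or fixed in its totals, and it names no stratification factor.

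Under *Power and statistical analysis* it states: "The sample size for this study is 150 participants with 75 participants in each arm (Lyprinol vs Placebo". The sample size assumes "a small to medium effect size (F = .20) on the Conners’ was postulated for Lyprinol over placebo", with six ratings up to week 18, and the analysis is repeated measures ANOVA with 75 per group. Chance imbalance is dealt with by one rule: variables that differ significantly between the groups at baseline are added as covariates.

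Under *Design*, children take "3 capsules (if less than or equal to 45 kg) or 4 capsules (if greater than 45 kg) of PCSO-524® or placebo". *Procedure* explains that weight rather than age decides the capsule count, because weight is held to affect digestion and absorption. Weight is therefore known before treatment is handed out, and the article itself regards it as relevant to the intervention.

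**The concern.** There are two separate points, of unequal weight.

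First, a random number generator without a stated restriction does not by itself produce 75 per arm. The article gives the result but not the feature of the list that would secure it.

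Second, and more important, the 45 kg rule divides the children into two regimens. Over an age range of 6 to 14 years, the heavier band will tend to hold the older children. Nothing in the stated allocation balances the bands between arms, and nothing in the stated model accounts for them. The covariate rule helps only once an imbalance is large enough to be significant. A smaller imbalance is left in the comparison, and the final model is unknown until the baseline data have been tested.

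The outcomes most exposed are secondary measures recorded in raw units, such as COMPASS reaction times and EEG measures, to the extent that they change with age. The background section on ADHD discusses maturation in connection with EEG. For COMPASS, age dependence is an assumption of this review.

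**Working it through.** **Inputs from the article.** N = 150, 75 per arm; f = 0.20; six time points; alpha 0.05; power 0.80; critical F 3.92; 118 before drop-out; about 20% drop-out; weight cut at 45 kg.

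**Assumptions not in the article.** Correlation between visits 0.5; share of children over 45 kg 10%, 20% or 30% (15, 30 or 45 of 150); a difference of 1 SD between the weight bands on an age-dependent score.

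**1. The plan's own figure.** For the between-group effect in a repeated measures ANOVA, lambda = f² × N × m / (1 + (m − 1) × rho) = 0.04 × 118 × 6 / 3.5 = 8.09, with 1 and 116 degrees of freedom. The critical F is 3.923 and the power 80.5%. Drop-out: 118 / 0.8 = 147.5, so 148, close to 150. The figure reproduces. It also shows that the powered test is the group effect averaged over all six visits.

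**2. Arm sizes if the list were simple.** With Binomial(150, 0.5):
- P(exactly 75:75) = 6.5%
- central 95% range of one arm: 63 to 87
- P(smaller arm is 65 or fewer) = 12.1%

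Power at 120 completers, using the effective size 4 × n1 × n2 / (n1 + n2):

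| Split | Effective N of 150 | Power |
|---|---|---|
| 75/75 | 150.0 | 81.2% |
| 63/87 | 146.2 | 80.2% |
| 60/90 | 144.0 | 79.6% |

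The loss is about 1 point at 63/87 and 1.6 points at 60/90, which is negligible.

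**3. Imbalance in weight band.** Let K be the number of children over 45 kg. For a simple list the split was simulated. For a list fixed at 75/75, the number a in one arm is hypergeometric, P(a) = C(K, a) × C(150 − K, 75 − a) / C(150, 75), and the gap in share is |2a − K| / 75.

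| Share over 45 kg | K | P(gap ≥ 10 points), simple list | P(gap ≥ 10 points), fixed 75/75 |
|---|---|---|---|
| 10% | 15 | 4.1% | 2.7% |
| 20% | 30 | 13% | 15.2% |
| 30% | 45 | 18% | 15.4% |

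Fixing the totals therefore does not balance the bands.

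**4. What the covariate rule would catch.** In equal arms, with a chi-square test without continuity correction:
- K = 15: the first significant split is 12 v 3, a gap of 9/75 = 12.0 points. The next smaller split, 11 v 4 (9.3 points), has p = 0.057.
- K = 30: the first significant split is 20 v 10, a gap of 13.3 points. There chi-square = 150 × (20 × 65 − 10 × 55)² / (30 × 120 × 75 × 75) = 4.17, p = 0.041. At 19 v 11 (10.7 points), chi-square = 150 × (19 × 64 − 11 × 56)² / (30 × 120 × 75 × 75) = 2.67, p = 0.10.
- K = 45: the first significant split is 29 v 16, a gap of 17.3 points.

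From the same hypergeometric distribution, a gap of 10 points or more that is not significant occurs in 8.7% of lists at K = 30 (the 19 v 11 split) and in 12.2% at K = 45 (27 v 18 and 28 v 17). At K = 15 it does not occur, because the first gap above 10 points is already significant.

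**5. Size of the effect.** A 10-point gap times a 1 SD band difference shifts the group contrast by 0.10 × 1 = 0.10 SD. For scale, f = 0.20 in two equal groups corresponds to d = 2 × 0.20 = 0.40, so the shift is a quarter of that. The 0.40 was postulated for the Conners' score, whereas the shift is argued for age-dependent secondary outcomes, so the ratio is only a yardstick.

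**The case against.** The strongest reply is that simple randomisation is nowhere stated. A pre-built list with a treatment number beside each participant number could hold a random order of 75 A and 75 B, or blocks, and a journal article commonly leaves that detail to the full protocol. This stands. A reader might infer that the method contradicts the 75 per arm. The documents do not support that: they fail to show how 75 per arm is secured, and little power depends on it.

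Next, the 45 kg rule is the same in both arms, so random allocation keeps the comparison unbiased, and chance imbalance is part of the error that the test already allows for. This also stands. A reader might infer that the treatment comparison is biased; it is not. What remains is noise that a known baseline factor could remove.

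Third, the outcomes are measured at baseline, and a stable level difference cancels from a change or group-by-time contrast. This holds for those contrasts. It does not hold for a group effect averaged over visits, and that is the effect to which the stated critical F of 3.92 corresponds. The article does not say which term will decide each outcome.

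Fourth, the covariate rule could bring in weight or age. It could, but only above the thresholds shown in the working. At a 10% share of heavier children it would catch every gap of 10 points or more.

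Finally, the share over 45 kg and the 1 SD difference are assumed, and no link between weight and the Conners' score is shown. This stands and limits the point to minor.

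**Conclusion.** The point holds as a minor one. The article does not show that its 75 per arm is secured, but even a simple list would cost only about 1 point of power at a 63/87 split. The more useful finding is that the 45 kg split, which the plan already treats as relevant, is left to chance in the allocation and missing from the stated model, while the stated remedy depends on a baseline significance test.

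With 20% to 30% of children over 45 kg (assumed), roughly 9% to 12% of equal-arm lists would carry a gap of 10 points or more that the rule would leave unadjusted. With 10% over 45 kg, none would. If the bands differ by 1 SD (assumed), a 10-point gap moves a group contrast by 0.10 SD.

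The consequence is avoidable imprecision, mainly for secondary outcomes that change with age. It would be tempting to conclude that the primary Conners' result is compromised. The documents give no relation between weight or age and that score, so this does not follow.

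**What to change.** Have the third party build the list in permuted blocks of varying, undisclosed size, separately for children at or below 45 kg and children above it, and say so under *Randomization and safety*. This holds each band's split to within half a block. Arm totals will then be close to 75 rather than exactly 75, and the text should say this.

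Under *Power and statistical analysis*, replace the significance-triggered covariate rule with weight band as a pre-specified fixed term in the primary and secondary models, kept whatever its baseline distribution.

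If the list is already restricted, one sentence settles the arm-size part; the model term is still worth adding.

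The cost is a slightly more complex list (two sequences instead of one) and one degree of freedom in the model. Weight must already be known to apply the capsule rule, so no extra measurement, visit or participant is needed, and the capsule rule itself is unaffected.

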#### Primary outcome

The CPRS will be used to record parents’ ratings of inattention and hyperactivity. The CPRS is to be filled out by the parent at home on weeks 2, 4, 8, 10, 14 and 18 [56]. Researchers involved exclusively in this trial will score and enter the data from each CPRS following the participants’ completion of the trial. The researchers are blinded to treatment allocation.

#### Secondary outcome measures

The Tests of Variables of Attention (TOVA) will assess symptoms of inattention and impulsivity. The TOVA is a computer-based assessment of inattention [54].

### COMPASS (computerised mental performance assessment system)

The COMPASS battery has been developed to include tests which have been shown to be sensitive to nutritional manipulations. The tasks in this study are designed to allow assessment across the major cognitive domains i.e. attention, working memory, secondary memory and executive function. Parallel versions of each of the following tasks allowed for multiple testing. Previous studies have used a similar customized battery in testing adolescents and their responses to dietary changes [57-63]. The following cognitive COMPASS tasks will be administered: Word presentation; Immediate word recall; Picture presentation; Simple reaction time; Choice reaction time; Numeric working memory; Delayed word recall; Delayed word recognition; Delayed picture recognition (see Table 2 for task descriptions).

**Table 2 T2:** COMPASS task descriptions and scoring

**Task**	**Task description**	**Task scoring**
Word presentation	Individual words are presented sequentially on the monitor. Stimulus duration was 1 s, as is the inter-stimulus interval.	
Immediate word recall	The participant is allowed 60 s to write down as many of the words as possible.	The task is scored for number of correct answers, errors and intrusions and the resulting score is converted into a percentage
Picture presentation	Twenty line-drawings of everyday items are presented on the computer screen. Stimulus duration is 3 s, with a 1 s inter-stimulus duration.	
Simple reaction time	A series of upwards pointing arrows appear in the centre of the screen with a randomly varying inter-stimulus interval between 1 and 3 s. The participant will press the space bar as quickly as possible to the on screen appearance of each stimulus.	The task is scored in Response times (recorded in milliseconds)
Choice reaction time	Arrows pointing to the left or right are presented in the centre of the screen with a randomly varying inter-stimulus interval of 1–3 s. The volunteer presses the corresponding ‘left’ or ‘right’ cursor key on the computer keyboard as quickly as possible.	The task is scored for accuracy (%) and reaction time (ms).
Numeric working memory	A series of five digits is presented on the computer screen sequentially for the participants to hold in their memory. This is followed by a series of 30 probe digits. The participants indicate whether or not the digit was from the original series by pressing corresponding keys labelled ‘yes’ and ‘no’. This is repeated three further times with different stimulus sets.	Reaction times (ms) and accuracy (% correct) are measured
Delayed word recall	Approximately 20 min after the word presentation, the participant is allowed 60 s to write down as many of the items from word presentation as possible.	The task is scored as for immediate word recall.
Delayed word recognition	Word recognition is tested by representation of the words from the original list randomly interspersed with an equal number of distracter words. Participants respond either ‘yes’ or ‘no’ by pressing corresponding key to indicate whether the word had previously been presented or not.	The task is scored for accuracy (%), and reaction time (ms).
Delayed picture recognition	Picture recognition is tested by the presentation of the original drawings and an equal number of distracters in random order. Participants respond either ‘yes’ or ‘no’ by key press in order to indicate whether the picture had been presented previously.	The task is scored for accuracy (%) and reaction time (ms).

### Mood

The Brunel Mood Scale (BRUMS) was derived from the Profile of Mood States mood scale [64] and contains 24 simple mood descriptors such as angry, energetic, nervous, and unhappy. The BRUMS (formerly known as the profile of Mood States – Adolescents or POMS-A) was designed for purely adolescent populations and the validation process can be found in Terry et al [55,65].

### Diet

At the beginning of the trial the parent will complete a Food Frequency Questionnaire (FFQ) that will provide a detailed description of the child’s food intake. In week 4 of the trial the parent will complete a 7-day food diary consisting of what the child has had to eat for breakfast, lunch and dinner as well as any significant snacks throughout those days. This diary will be compared to the FFQ to determine any changes in diet that may have occurred while in the study.

### Resting electroencephalography (EEG) and steady state topography (SST)

Brain electrical activity will be recorded from 64 sites on the scalp, including all of the International 10–20 positions and sites located midway between the 10–20 locations. All electrodes will be held in place using an electrocap. Electrode impedance will vary from 2.5 kohmsto 8.5 kohms when measured at 40 Hz. The average of both earlobes will serve as a reference. EEG will be amplified and bandpass filtered (3 dB down at 0.1 Hz and 30 Hz) prior to digitisation to 12-bit accuracy at a rate of 200 Hz. Changes in brain wave ratios in key areas of activity will also be examined to test the hypothesis that Lyprinol® will ameliorate the cortical hypoarousal that has been associated with ADHD [11,53,66-71]. The stimulus used to evoke the SST will be a diffuse 13 Hz sinusoidal flicker superimposed on the visual field by a pair of goggles. The goggles will comprise two half-silvered mirrors that reflect two light-emitting diode arrays over the subject’s visual field, subtending a horizontal angle of 160 degrees and a vertical angle of 90 degrees. The maximum intensity at the peak of the stimulus waveform will be 5.0 cd/m^2^ and the modulation depth will be 45%. In order to control for variations in vigilance, subjects will perform a low level cognitive task.

#### Signal processing of EEG data

Two hundred and fifty seconds of EEG data will be gathered for each subject in each condition, yielding a frequency resolution of 0.004 Hz. The SST recorded at each electrode will be determined via Fourier analysis centred at 13 Hz with a width of 0.004 Hz. The sine and cosine Fourier components will be used to determine the amplitude and phase of the SST [72]. Data will be checked for artefact using techniques described in Silberstein et al., (1995) [73].

### Global clinical impression scale (GCI)

Amongst the most widely used of extant brief assessment tools in psychiatry, the GCI is a 3-item observer-rated scale that measures illness severity (CGIS), global improvement or change (GCIC) and therapeutic response. The GCI has proved to be a robust measure of efficacy in many clinical drug trials, and is easy and quick to administer. The GCI is rated on a 7-point scale, with the severity of illness scale using a range of responses from 1 (normal) through to 7 (amongst the most severely ill patients). GCIC scores range from 1 (very much improved) through to 7 (very much worse). Treatment response ratings should take account of both therapeutic efficacy and treatment-related adverse events and range from 0 (marked improvement and no side-effects) and 4 (unchanged or worse and side-effects outweigh the therapeutic effects). Each component of the GCI is rated separately; the instrument does not yield a global score.

#### Power and statistical analysis

The sample size for this study is 150 participants with 75 participants in each arm (Lyprinol vs Placebo). A power calculation to determine the sample size was performed using Gpower 3.12. Based on previous studies looking at omega-3 supplementation in children with ADHD such as Sinn & Bryan (2007) who had an *n* of 132 and were able to find statistical significance in terms of the CPRS [15], a small to medium effect size (F = .20) on the Conners’ was postulated for Lyprinol over placebo from baseline to week 18 over six time points (critical F = 3.92, with an alpha probability of 0.05 and beta power of 0.80). This provided a sample size of 118; with drop-outs being projects at approximately 20%, a sample of 150 participants was estimated. Repeated Measures ANOVAs with an *n* of 150 (75 per group) will allow the researchers to account for any confounding variables in the trial including within-group and between-group variability. Any heterogeneous variables showing statistically significant differences at baseline will be co-varied in order to negate their influence on the power of the study.

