**Methods:**

A randomized double blind placebo controlled trial will be utilized to assess the effects of 14 weeks administration of Lyprinol/Omega XL versus placebo in 150 children aged 6 to 14 years with high levels of hyperactivity and inattention. Additionally, a range of cognitive, mood and central electrophysiological measures will be undertaken during the 14 week supplementation trial. The primary outcome measure, the Conners’ Parent Rating Scales will be completed initially at baseline, then in weeks 4, 8, 10, 14 and then again at 4 weeks post-administration (week 18). The results will contribute to our understanding of the efficacy of marine based Omega-3 s with high anti-inflammatory actions on inattention and hyperactivity in children aged 6 to 14 years.

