### Post-treatment period: follow up

Participants’ parents will complete the CPRS and the Brunel Mood Scale four weeks following the cessation of Active or placebo administration to determine any changes in mood or behaviour since ceasing treatment. These scales can be completed by the parents independently or (more usually) with the child. Participants will be questioned non-specifically for any Adverse Events (AEs). A review of their Symptom Checklists will also help to determine if a participant experienced an AE. Figure 1 describes the flow of data collection for this study.

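### The sample size of 118 is powered for an arm difference averaged over six CPRS ratings, one of them the pre-treatment baseline; for a 0.40 SD effect that begins after baseline, that test has about 65% power, not 80%

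*Protocol article*

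**What the plan says.** Under Power and statistical analysis, the Protocol article gives the size of the assumed effect as "a small to medium effect size (F = .20"). The comparison and time span that it applies to are described as "postulated for Lyprinol over placebo from baseline to week 18 over six time points (critical F = 3.92"). Alpha is set at 0.05 and power at 0.80. The result is reported in these words: "This provided a sample size of 118". An allowance of about 20% for dropout then raises the target to "150 participants with 75 participants in each arm". The analysis is described only as repeated measures ANOVA. Neither the term to be tested nor the correlation between ratings is given.

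The six CPRS ratings are the baseline and those taken "then in weeks 4, 8, 10, 14 and then again at 4 weeks post-administration (week 18"). Table 1 and the Procedure section place the baseline at the week 2 centre visit, where children are tested and then allocated, before the 14 weeks of capsules begin. The post-treatment follow-up section says that the week 18 scales are collected "to determine any changes in mood or behaviour since ceasing treatment". The study aims, however, describe the primary aim as covering symptom levels before, during and after the intervention, and the Primary outcome section lists week 18 among the CPRS ratings.

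**The concern.** The printed critical F shows which test was powered. A value of 3.92 at this sample size has one numerator degree of freedom, so it is not the six-point group-by-time test. It fits the group main effect, which gives every rating equal weight. A rating taken before the first capsule cannot carry a treatment effect, so including it as an outcome level pulls the averaged difference towards zero.

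This calculation is the only justification given for the enrolment target. If the postulated 0.40 SD is meant as what the supplement does once children are taking it, the quoted 80% overstates the chance that this test detects it. The paragraph also leaves a reader unable to tell which test the 80% was meant for.

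**Working it through.** **Inputs from the protocol.** f = 0.20 (for two equal arms d = 2f = 0.40 SD); m = 6 ratings; alpha 0.05; power 0.80; critical F 3.92; N = 118 before dropout.

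**Assumed.** The correlation ρ between ratings is not stated; 0.5 is used because it returns 118, and 0.3 and 0.7 are shown as a range. Equal variances and equal correlations across ratings (compound symmetry) are also assumed.

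**Step 1: reproduce 118 and 3.92.** For the group main effect, the noncentrality is λ = f²·N·m / (1 + (m − 1)ρ), with df 1 and N − 2.

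λ = 0.04 × 118 × 6 / (1 + 5 × 0.5) = 28.32 / 3.5 = 8.09. Critical F(1,116) = 3.923 and power = 0.805. Both printed figures are recovered. With f and m fixed, other correlations give other totals: 84 at 0.3, 102 at 0.4, 134 at 0.6, 150 at 0.7 and 166 at 0.8.

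The alternatives do not fit:
- Group-by-time over six ratings, f = 0.20, ρ = 0.5: N = 28, critical F 2.28. At N = 118 its critical F(5,580) is 2.23.
- Group-by-time over two ratings: N = 52, critical F 4.03.
- A single rating: N = 200.
- Group main effect over 5 or 4 ratings at ρ = 0.5: N = 120 or 126.

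The dropout step is sound: 118 / 0.8 = 147.5, so 148, rounded up to 150.

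**Step 2: let the effect start after baseline.** Suppose d = 0.40 at all five later ratings and 0 at baseline. The six-rating average is 0.40 × 5/6 = 0.333 SD, so f = 0.1667 and λ falls by (5/6)². At ρ = 0.5, λ = 8.09 × 0.694 = 5.62 and power is 65%. If the effect has gone by week 18, the average is 0.40 × 4/6 = 0.267 SD, λ = 8.09 × 0.444 = 3.60 and power is 47%.

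Power of the six-rating main effect at N = 118:

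| Pattern of the difference | ρ = 0.3 | ρ = 0.5 | ρ = 0.7 |
|---|---|---|---|
| 0.40 SD at all five later ratings | 79% | 65% | 55% |
| 0.40 SD on treatment, none at week 18 | 60% | 47% | 38% |

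If all 150 children completed, the two cases at ρ = 0.5 would have 76% and 57%.

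**Step 3: the effect that the 80% implies.** For the six-rating average to equal 0.40 SD with zero at baseline, the difference at each of the five later ratings must be 0.40 × 6/5 = 0.48 SD.

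**Step 4: the group-by-time test, in case that was intended.** λ = N·Σ(δⱼ/2)² / (1 − ρ), where δⱼ is the arm difference at rating j minus its six-rating mean. For 0.40 SD at all five later ratings, the deviations are −0.333 once and +0.067 five times, so Σδⱼ² = 0.1111 + 0.0222 = 0.1333. Then λ = 118 × 0.0333 / 0.5 = 7.87 on 5 and 580 df: power 55% at ρ = 0.5, and 81% at 0.7.

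**Step 5: the same children, with baseline as a covariate.** For the mean of k later ratings adjusted for baseline, the residual variance is v = (1 + (k − 1)ρ)/k − ρ², and λ = N·(d/2)²/v. At d = 0.40 and ρ = 0.5:
- Four on-treatment ratings: v = 0.625 − 0.25 = 0.375, λ = 118 × 0.04 / 0.375 = 12.59, power 94%.
- Week 14 alone: v = 1 − 0.25 = 0.75, λ = 6.29, power 70%.

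**The case against.** Three points against the concern carry weight.

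First, the 80% is arithmetically right if f = 0.20 is defined as the average over all six ratings, and the sentence can be read that way. This stands, but the plan is then assuming 0.48 SD at every later rating, because the baseline contributes nothing.

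Second, the protocol never says that the group main effect is the term to be tested. The critical F shows what was powered, not what will be reported, and an analysis plan that is not shown may name group-by-time. That also stands. In that test the baseline is the reference level and does not dilute the effect. It is nevertheless a different test, with 5 numerator df, and the stated power was not calculated for it.

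Third, a reader might infer that week 18 plainly does not belong in the primary test and that true power is therefore 47% or lower. The documents do not support that. The follow-up section treats week 18 as an off-treatment question, but the stated aim includes the period after the intervention and the primary outcome lists that rating. No effect trajectory or carry-over assumption is given, so the 47% is an illustration. Only the baseline part follows from the design itself.

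**Conclusion.** The point holds for the baseline rating. The calculation behind 118 treats a pre-treatment measurement as one of six equally weighted outcomes. If 0.40 SD is the effect once treatment has started, and it lasts fully to week 18, the powered test has about 65% power at 118 completers and correlation 0.5. The shortfall depends on the unstated correlation: it almost vanishes at 0.3 (79%) and is larger at 0.7 (55%). Power is lower still if the effect fades by week 18.

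A reader might go further and conclude that 150 children are too few. That does not follow: the same 118 completers give about 94% power for the baseline-adjusted mean of the four on-treatment ratings under the same assumptions. The fault is that the quoted power belongs to a poorly chosen contrast. These figures rest on compound symmetry, on the inferred correlation and on reading 0.40 SD as the post-baseline effect.

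**What to change.** State the primary treatment contrast as the arm difference in post-baseline CPRS, with baseline CPRS as a covariate and not as an outcome level. Say explicitly whether week 18 is part of that contrast or a separate off-treatment question; the aims and the follow-up section point different ways, and the choice is the sponsor's. Settle both before unblinding.

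Then replace the power sentence with the power of the chosen contrast at about 118 to 120 completers, and state the assumed correlation. At 0.40 SD and correlation 0.5, for example, this would be about 94% for the mean of the four on-treatment ratings or about 70% for week 14 alone. If group-by-time was the intended test, say so and give its power instead.

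The cost is a reworded analysis paragraph and a new power figure, with no extra children or visits. If week 18 is made a separate question, it no longer contributes to the primary test.

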### Participants

One hundred and fifty children aged between 6 and 14 years will complete either 14 week consumption of Lyprinol/Omega XL or placebo. This age range is one of the most common developmental stages for children to experience increased levels of hyperactivity, impulsivity and inattention and where 5-12% of children will receive a diagnosis of ADHD. The study was ethically approved by the Swinburne University Human Research Ethics Committee (SUHREC Project 2010/175) and all participants will provide written informed consent. All procedures will be conducted in accordance with the Declaration of Helsinki (2008) and the good clinical practice (GCP) guidelines. The trial has been registered with the Australian and New Zealand Clinical Trials Registry (ACTRN12610000978066).

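### Repeated measures ANOVA with n = 150 does not fit the plan's own 20% drop-out: as stated, and without imputation, it would compare about 120 completers rather than the 150 children randomised

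*Protocol article*

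**What the plan says.** Under Power and statistical analysis, the protocol article derives 118 children for 80% power and then allows for loss: "with drop-outs being projects at approximately 20%, a sample of 150 participants was estimated". The next sentence names repeated measures ANOVAs as the analysis and attaches to them an n "of 150 (75 per group) will allow the researchers to account for any confounding variables in the trial".

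The Participants section gives the same 150 as the number finishing treatment: "One hundred and fifty children aged between 6 and 14 years will complete either 14 week consumption".

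The effect is postulated "from baseline to week 18 over six time points". The Primary outcome section gives the schedule: "The CPRS is to be filled out by the parent at home on weeks 2, 4, 8, 10, 14 and 18". The Centres section and Table 1 place only weeks 4, 10 and 18 at home, with weeks 2, 8 and 14 at the centre. The article names no imputation, mixed model or other device for keeping a child with an incomplete set of ratings in the ANOVA.

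**The concern.** The number recruited, the number expected to finish and the number entering the ANOVA are treated as one figure, 150. With 20% drop-out they cannot be the same, unless incomplete children are kept in by some means that the article does not state.

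The choice of method matters here. Classical repeated measures ANOVA works on a complete child-by-visit table. A child with five of six CPRS ratings is removed and the five are discarded. The week-18 rating comes four weeks after treatment ends, so even a child who finished all 14 weeks is lost if that form is missing. The Procedure section lets parents hand in forms at each session or at the end of the study, so a family that leaves may never return forms already filled in.

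Two things are at stake in the primary comparison. First, children who stop because the capsules seem not to help or are not tolerated would be left out. If that happens differently in the two arms, the groups compared are no longer those formed by randomisation, and the estimate may be biased in a direction that cannot be known in advance. Second, every missed single form costs a whole child, and the allowance for this is thin.

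**Working it through.** **Inputs from the article (Power and statistical analysis):** effect size f = 0.20; m = 6 ratings; alpha 0.05; power 0.80; critical F 3.92; 118 children before drop-out; about 20% drop-out; 150 in total, 75 per arm.

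**Assumed:** correlation between a child's ratings ρ = 0.5. The article gives no value.

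**1. Reproduce the plan's figure.** For the between-group F test of a repeated measures ANOVA:

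λ = f² × N × m / (1 + (m − 1)ρ), with 1 and N − 2 degrees of freedom.

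- At N = 118: λ = 0.04 × 118 × 6 / 3.5 = 8.09; critical F(1, 116) = 3.92; power 80.5%.
- At N = 116: power 79.9%.

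So 118 is the smallest even N that reaches 80%, and both 118 and 3.92 reproduce. Other correlations do not give 118: ρ = 0.4 needs 102 and ρ = 0.6 needs 134. The group-by-time interaction test needs only 28 children with critical F 2.28, so it is not the test that was powered.

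**2. Drop-out inflation.** 118 / 0.80 = 147.5, so 148. The stated 150 is sound.

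**3. Number the ANOVA would analyse.** 150 × (1 − 0.20) = 120, about 60 per arm, not 75. The inflation in step 2 itself treats a drop-out as contributing no data.

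**4. Power at that number (same formula).**

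| N | λ | Power |
|---|---|---|
| 150 | 10.29 | 89.0% |
| 120 | 8.23 | 81.2% |
| 118 | 8.09 | 80.5% |

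At exactly 20% loss the planned 80% is kept. The margin is 120 − 118 = 2 children.

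**5. Missed single forms on top of drop-out.** Suppose each of the five post-baseline forms is missed independently with probability q among the 120. Complete cases are 120 × (1 − q)⁵. The values of q are assumptions; the article gives none.

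| q | Complete cases | Power |
|---|---|---|
| 0 | 120 | 81% |
| 1% | 114 | 79% |
| 2% | 108 | 77% |
| 3% | 103 | 75% |
| 5% | 93 | 70% |

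**6. Milder version.** If only the three home forms (weeks 4, 10 and 18) can be missed, complete cases are 120 × (1 − q)³. For q = 1%, 3% and 5% this gives about 116, 110 and 103 children, with power 80%, 78% and 75%.

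**The case against.** The strongest reply is that the article names a family of analyses and says nothing of deleting incomplete children. Analysis sets and missing-data rules commonly sit in a fuller document that is not shown here, and with imputation an ANOVA on 150 is possible. This stands as a limit. It would be too strong to say that n = 150 can never occur, and the absence of a missing-data section is not the point. What remains is that the stated method and stated n do not fit the drop-out projected one sentence before, and that the Participants section repeats the conflict.

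A reader might infer that the trial is too small, with the analysed number below 118. The article does not support that: at its own 20% drop-out, 120 remain. The fall below 118 needs further missed forms at assumed rates. Independent misses are also the harsh case, since missed forms tend to cluster in the same children. The 20% could even be read as covering every child lost to the analysis.

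Two other readings are tempting and should be set aside:

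- **Sphericity.** The test that reproduces 118 and critical F 3.92 is the between-group test, which uses each child's mean and does not rest on sphericity. Unequal visit spacing is not in itself a violation.
- **Confounding.** The sentence on accounting for confounding variables is loosely worded. The article goes on to mention within-group and between-group variability and covariate adjustment for baseline differences, so it does not support a separate charge.

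It is also fair to say that the size and direction of any bias cannot be derived from the article.

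**Conclusion.** The point holds in a limited form. The article pairs repeated measures ANOVA and n = 150 with about 20% drop-out. As stated, and absent imputation, the primary comparison would rest on about 120 completers, and whatever ratings the other 30 or so children supplied would be thrown away. Bias is a risk if leaving is related to benefit or tolerability; its size is unknown.

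The sample size calculation is not at fault. Power at exactly 20% loss is about 81%, given f = 0.20 and an assumed ρ = 0.5, the value that reproduces the article's own 118. The weakness is that the method turns each missed form into a lost child, with two children to spare. The range of 79% to 70% power rests on assumed, independent miss rates of 1% to 5% on each of five forms.

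**What to change.** - **Method.** For the CPRS, replace repeated measures ANOVA by a likelihood-based mixed model for repeated measures. Include all randomised children with any post-baseline CPRS, in their randomised arm. Fit arm, visit, arm-by-visit, baseline CPRS and baseline-by-visit, with unstructured covariance. Children with no post-baseline rating still fall out, so their number should be reported by arm.
- **Primary contrast.** Prespecify the arm effect averaged over the post-baseline visits. This stays close to the between-group test that was powered. It is not identical, because baseline becomes a covariate and is no longer one of the six ratings, so recheck the power statement for this contrast.
- **Wording.** In the Participants and the Power and statistical analysis sections, state 150 randomised and about 120 expected to complete.

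The cost is some redrafting, one power check and a little more analysis work in standard software. No extra children or visits are needed for the change of method itself. It should be settled before unblinding.
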